## Abstract

**Background:**

Fractures of the proximal humerus are common injuries and account for 4–5 percent of all fractures, second only to hip and wrist fractures. The incidence is positively correlated with age and osteoporosis, and is likely to increase. Displaced four-part fractures are among the most severe injuries, accounting for 2–10 percent of proximal humeral fractures. The optimal intervention is disputed. Two previous randomised trials were very small and involved a noticeable risk of bias, and systematic reviews consequently conclude that there is inadequate basis for evidence-based treatment decisions. We aim to compare the effect of osteosynthesis with angle-stable plate with non-surgical management, and the effect of primary hemiarthroplasty with both osteosynthesis and non-surgical management.

**Methods/Design:**

We will conduct a randomised, multi-centre, clinical trial including patients from ten national shoulder units within a two-year period. We plan to include 162 patients. A central randomisation unit will allocate patients. All patients will receive a standardised three-month rehabilitation program of supervised physiotherapy regardless of treatment allocation. Patients will be followed at least one year. The primary outcomes will be the overall score on the Constant Disability Scale, and its pain subscale, measured at 12 months. A blinded physiotherapist will carry out the assessments. Other secondary outcomes are Oxford Shoulder Score, and general health status (Short Form-36).

## Background

Fractures of the proximal humerus are common injuries and account for 4–5 percent of all fractures[1,2]. The incidence is expected to increase due to its association with advanced age and osteoporosis [3-5]. Displaced four-part fractures are among the most severe injuries accounting for 2–10 per cent of all proximal humeral fractures [6-8] and for about one out of four operated proximal humeral fractures[9].

The optimal treatment for displaced four-part fractures is disputed. Several surgical techniques have been suggested including transcutaneus reduction, external fixation, hemiarthroplasty or open reduction and internal fixation with Kirschner wiring, tension-band wiring, transosseous suturing, plate fixation, intramedullary rod fixation, screw fixation, or, most recently, angle-stable plates. Numerous clinical series have been published, but most techniques have shown unsatisfactory results except in 'valgus impacted' fracture patterns (Fig. 1) or in selected younger populations [10-14].

**Figure 1 F1:**
[figure not shown]
**Two patterns of displaced four-part fractures**. Reprinted from Murray and Zuckerman [18].

Two previous very small randomised clinical trials compared treatments for displaced four-part fractures. Stableforth[8] compared arthroplasty with non-surgical management on 32 patients. The result tended to favour surgery. Hoellen[15] compared arthroplasty with osteosynthesis on 30 patients, but found no statistically significant difference in outcome. Both trials had low power, and did not report clearly adequate concealment of patient allocation or blinding procedures. The trials were analysed and summarised in a Cochrane review[16] that emphasised that the limited evidence available does not even confirm that surgery is preferable to conservative treatment in displaced fractures. Other systematic reviews have concluded that published data are inadequate for evidence-based decision making[6,17].

### Aims

Our primary aim is to compare the effect of osteosynthesis with angle-stable plate with non-surgical management for displaced four-part fractures in elderly. We also aim to compare the effect of primary hemiarthroplasty with both osteosynthesis and with non-surgical management.

Our secondary aim is to study prognostic differences between two pathoanatomical patterns of displaced four-part fractures: 'valgus impacted' four-part fractures and 'classical' four-part fractures (Fig. 1) [18].

## Methods/design

A randomised, multi-centre, national, clinical trial.

### Inclusion criteria

We will include patients diagnosed with a displaced four-part fracture within a two-year recruitment period from ten Danish hospitals providing advanced shoulder service. Eligibility criteria will be: age ≥ 60 years, patients mentally alert and physically fit (ASA-group 1–3) for surgery and rehabilitation.

The diagnoses of four-part fractures will be based on plain radiographs (at least two perpendicular views) and any available supplemental imaging material (CT or 3D CT). At least two consenting experienced shoulder surgeons should classify the fracture as a displaced four-part fracture. The timing of the classification, and the subsequent recruitment procedure, will be such that an operation can be conducted within two weeks of injury.

### Exclusion criteria

We will exclude patients with fracture-dislocations, head-splitting fractures, previous shoulder surgery, chronic shoulder pain, abuse problems, and patients unable to understand instructions in Danish and follow the rehabilitation protocol at their local hospital.

### Randomisation and concealment of allocation

After obtaining informed consent patients will be included in the trial and randomly allocated to three groups of equal size:

• Non-surgical management (physiotherapy and self-training).

• Osteosynthesis with angle-stable plate followed by physiotherapy and self-training. If osteosynthesis during the operation is regarded surgically impossible by the operating surgeon the operation will be converted to primary modular hemiarthroplasty.

• Primary modular hemiarthroplasty followed by physiotherapy and self-training.

The randomisation sequence will be computer generated. A remotely placed randomisation unit, otherwise not involved in the study, will irreversibly include patients into the trial before allocating them to treatment groups, communicating the result to the recruiting surgeon through telephone.

After randomisation the patients and surgeon involved will be informed about the patient's allocation to either non-surgical management or to surgical management, but they will not be informed about the type of surgery. The surgical procedure (osteosynthesis or hemiarthroplasty) will be revealed to the operating team just before the operation.

### Interventions

Surgery will be performed within 14 days of injury by a trained shoulder surgeon familiar with both surgical interventions. Operative techniques follow standardised instructions.

All patients will receive a standardised rehabilitation program of supervised physiotherapy and instructed self-training regardless of treatment allocation. The local physiotherapists will be involved in the assessment of the outcome after 12 months and will record compliance with the rehabilitation program.

### Evaluation

All patients will be followed actively for one year post injury. They will be seen by the responsible shoulder-surgeon in the out-patient clinic at two weeks, six months and 12 months. All patients will be radiographed (at least two plain perpendicular radiographs) prior to each visit. Clinical outcome assessment will be performed after six and 12 months by a blinded central physiotherapist not involved in the rehabilitation of the patient. In addition, the local physiotherapists will assess outcome after 12 months. The evaluation procedure will follow a standardised protocol.

Patients will be followed up after three years. No clinical assessment will be carried out, but data on complications that may have developed after the 12 months evaluation is extracted from the clinical databases at each hospital (discharge letters, discharge diagnosis, and if needed journal notes).

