### Patient drop-out and protocol violations

Patients who drop-out of the trial will be recorded, and the reason for drop-out will be noted. Patients that do not comply with self-training and physiotherapy will be recorded. Patients that cross-over from one treatment group to another (non-surgical management to secondary hemiarthroplasty or osteosynthesis to primary hemiarthroplasty) will be recorded.

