### Side-effects reporting

We will record any case of deep infection, nerve injury, implant malposition, heterotopic ossification, avascular necrosis, malunion, nonunion, instability, dislocation, implant removal and revision surgery. We also record any case of pulmonary embolism, other medical complications, and death by any cause during the follow-up period.

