### Statistical analysis plan

#### Sample size and power calculation (ANOVA)

To have an 80% chance of detecting as significant (at the 5% level) a ten point difference or more in mean total Constant score between the three groups, with an assumed standard deviation of 15 points and a loss to follow up of 10 patients in each group, a total of 162 patients is required.

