### Research plan

Start date: April 2009

Finish date of recruitment: March 2011

Finish date of follow-up: March 2012

Submission date of paper: August 2012

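### The three-year hospital-record extraction is worded to start after the 12-month evaluation, which leaves complications between drop-out and month 12 with no stated source

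*Protocol article*

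**What the plan says.** The Evaluation section of the protocol article describes two stages of follow-up.

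- **First year.** "All patients will be followed actively for one year post injury". The contacts named are clinic visits: "They will be seen by the responsible shoulder-surgeon in the out-patient clinic at two weeks, six months and 12 months", each preceded by radiographs, plus outcome assessments by physiotherapists.
- **Three years.** There is no clinical assessment. Instead, "data on complications that may have developed after the 12 months evaluation is extracted from the clinical databases at each hospital".

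Four other sections bear on the same events.

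- **Side-effects reporting** is unrestricted: "We will record any case of deep infection, nerve injury, implant malposition", followed by further shoulder complications. A second sentence adds pulmonary embolism, "other medical complications, and death by any cause during the follow-up period". It names no data source, does not exclude drop-outs and does not define the period.
- **Patient drop-out and protocol violations** says: "Patients who drop-out of the trial will be recorded, and the reason for drop-out will be noted". It does not say how events after drop-out are found.
- **Sample size and power calculation (ANOVA)** allows for "a loss to follow up of 10 patients in each group".
- **Data-analysis** reserves a three-year report for a separate publication. That report compares, by group, how many patients died or had shoulder surgery, with no lower limit at month 12.

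**The concern.** The extraction is the only source described that does not depend on the patient attending, and its stated lower limit is the 12-month evaluation. Take a patient who stops attending after the two-week visit and has revision surgery in month 4. No later visit records the event, and it predates the extraction window. If the 12-month evaluation never takes place, the window has no defined starting point for that patient.

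At stake are the by-group harm counts. The three-year comparison of deaths and shoulder surgery reads as cumulative from randomisation, so it needs complete first-year ascertainment. If drop-out differs between arms, or is related to complications, the missing events would not be spread evenly. No primary or secondary efficacy outcome is affected.

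**Working it through.** **1. The plan's own figure.** The only stated number connected with drop-out is the total of 162 with 10 lost per group. Inputs from the sample size section: 80% power, 5% level, 10-point difference, SD 15. Three equal groups come from the randomisation section. Assumed: group means of 0, 5 and 10.

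- One-way ANOVA power (noncentral F) with 44 per group is 79.6%; with 45 per group it is 80.6%.
- 3 × (44 + 10) = 162; 3 × (45 + 10) = 165.

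The figure reproduces within rounding and is not in dispute. It implies an allowance of 10/54 = 30/162 = 18.5%.

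**2. Which events have a stated route of capture?** For a patient who drops out at time t before month 12:

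| Interval | Stated route |
|---|---|
| Randomisation to t | First-year visits and recording |
| t to month 12 | None stated |
| Month 12 to three years | Record extraction, which needs no visit (start undefined if there was no 12-month evaluation) |

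Only the middle row is exposed. It lasts at most about 52 − 2 = 50 weeks, for a patient lost straight after the two-week visit and assuming no other contact reveals the event. Data-analysis keeps patients lost after six months by carrying their six-month value forward. If the planned 10 per group are the patients who cannot be analysed (an inference), each has at least six months exposed.

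**3. Possible size, on assumptions only.** The document gives no complication rate and no drop-out timing. Let d be the proportion dropping out before month 12, r the first-year event rate in drop-outs relative to other patients, and f the share of a drop-out's first-year events that fall after drop-out. The share of all first-year events in the exposed interval is

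d·r·f / (d·r + 1 − d).

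| d | r | f = 0.25 | f = 0.75 |
|---|---|---|---|
| 10/54 = 18.5% | 1 | 4.6% | 13.9% |
| 10/54 = 18.5% | 2 | 7.8% | 23.4% |
| 5/54 = 9.3% | 1 | 2.3% | 6.9% |
| 5/54 = 9.3% | 2 | 4.2% | 12.7% |

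Worked example: d = 0.185, r = 2, f = 0.75 gives 0.278/1.185 = 23.4%. Only d = 18.5% comes from the plan, and it is borrowed from the Constant score calculation. The other values are illustrative.

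**4. The dates.** Recruitment ends in March 2011. One year later is March 2012, which is what the Research plan gives: "Finish date of follow-up: March 2012". Three years after the last entry would be March 2014, which belongs to the separate three-year publication. The term follow-up period in Side-effects reporting could mean either the one-year or the three-year span.

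**The case against.** The strongest reply is that the document never says first-year harms come only from visits, and never bars the use of records in that year. Side-effects reporting commits to every case without excluding drop-outs, and the extraction sentence may describe only what the three-year contact adds. Other contacts could reveal events: three months of supervised physiotherapy, the recorded reason for drop-out, and the recording of cross-overs to secondary surgery. First-year ascertainment after drop-out is also detail that an article may leave to the full protocol.

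Much of this stands. The text leaves the source for the exposed interval unstated; it does not say that these events go uncollected. What does not fall away is that the article states a lower limit for the extraction. Moving that limit changes a stated rule rather than supplying an omitted detail.

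Three stronger readings are tempting and are not supported:

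- **That all events in early drop-outs are lost.** Events before drop-out belong to first-year recording, and those after month 12 are within reach of the extraction.
- **That the bias can be read off by comparing completers with everyone.** Assume 20% in 44 completers and 40% in 10 drop-outs: (44 × 0.20 + 10 × 0.40)/54 = 23.7%, against 20%. This treats every drop-out event as unseen and removes drop-outs from the denominator, which no section does. With all 54 retained, the observed figure would be 44 × 0.20/54 = 16.3%. Both rates are assumptions.
- **That the March 2012 date conflicts with the follow-up described.** It equals the end of one-year follow-up for the last patient.

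**Conclusion.** The point holds as a cheap improvement to harms ascertainment. Followed literally, the protocol gives no source for complications between drop-out and month 12, and no start of the extraction window for patients without a 12-month evaluation. Its side-effects section promises every case, and its three-year analysis needs full counts.

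The size cannot be established from the document. The illustrative range of about 2% to 23% of first-year events rests on assumed event rates and drop-out timing, and on a loss allowance made for a different purpose. A reader might infer that harms are under-counted precisely in those most likely to have them. Drop-out after a severe fracture could be related to complications, but the document shows no such link, so this remains a possibility. The term follow-up period needs one stated meaning.

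**What to change.** - In Evaluation, run the planned hospital-record extraction from randomisation to three years for every randomised patient, including drop-outs as far as their consent allows.
- Report the three-year harm counts by randomised group, with all randomised patients as denominator.
- In Side-effects reporting, state whether the follow-up period means one year or three years.
- Leave the March 2012 date in the Research plan as it is. Replacing it with March 2014 would put the end of follow-up after the August 2012 paper submission in the same list.

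**Cost.** The same hospitals' records are already to be searched, so the main change is one start date. The downside is some extra extraction time and a check that consent covers record access after drop-out. The three-year extraction comes too late for the paper planned for August 2012. Completing the 12-month counts in that paper would need an earlier extraction, at additional cost. The extraction also still finds only what the participating hospitals' records contain.

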### Outcome measures

Clinical outcome is evaluated using an observer administered shoulder-specific score (Constant Disability Scale)[19,20], a patient administered shoulder-specific questionnaire (Oxford Shoulder Score)[21], and a patient administered general health status questionnaire(Short Form-36)[22,23].

The primary outcomes are

• Constant Disability Scale – total score (0–100 points) at 12 months

• Constant Disability Scale – pain subscale score (0–15 points) at 12 months

Secondary outcomes are

• Shoulder function. Oxford Shoulder Score – total score (12–60 points)

• General health. Short Form-36 questionnaire – total score (0–100 points)

### Patient drop-out and protocol violations

Patients who drop-out of the trial will be recorded, and the reason for drop-out will be noted. Patients that do not comply with self-training and physiotherapy will be recorded. Patients that cross-over from one treatment group to another (non-surgical management to secondary hemiarthroplasty or osteosynthesis to primary hemiarthroplasty) will be recorded.

### Side-effects reporting

We will record any case of deep infection, nerve injury, implant malposition, heterotopic ossification, avascular necrosis, malunion, nonunion, instability, dislocation, implant removal and revision surgery. We also record any case of pulmonary embolism, other medical complications, and death by any cause during the follow-up period.

### Statistical analysis plan

#### Sample size and power calculation (ANOVA)

To have an 80% chance of detecting as significant (at the 5% level) a ten point difference or more in mean total Constant score between the three groups, with an assumed standard deviation of 15 points and a loss to follow up of 10 patients in each group, a total of 162 patients is required.

#### Data-analysis

No interim data-analysis will be carried out. The data-analysis will be conducted by a biostatician at the end of the follow-up period.

Patients randomised to the non-surgical management group but who cross-over and undergo secondary surgery will primarily be analysed as they were randomised. Similarly, patients randomised to osteosynthesis but due to surgical technical difficulties are treated with primary hemiarthroplasty, will be analysed as randomised.

Patients that drop-out after the six months evaluation will be included in the analysis based on six months data ('last observation carried forward'). Drop-out of patients before the six months evaluation cannot be included in the analysis.

Descriptive statistics (mean and standard deviations, as well as median and 10 and 90 percentiles for continuous variables, and frequency and 95 percent confidence interval for binary variables) will be calculated for each of the three groups, and their relevant subgroups, at both time points. Relevant subgroups include:

• Valgus-impacted versus classical four-part fractures

• Cross-overs from non-surgical treatment to secondary hemiarthroplasty versus non cross-overs in non-surgical treatment group

• Cross-overs from osteosynthesis to primary hemiarthroplasty versus non cross-overs in osteosynthesis group.

Continuous and binary baseline characteristics will be tabulated according to the three treatment groups. No statistical testing will be performed, but relevant imbalances will be noted and reported. Baseline characteristics include: age, ASA Score, patient's treatment preference, surgeon's treatment preference and fracture pattern (valgus-impacted or classical four-part).

The primary analyses of effect will be two analyses of variance (ANOVA) based on the overall Constant scores, and the Constant pain subscale score, measured at 12 months. We will use the last observation carried forward approach, excluding patients only because of missing data, and analyse all patients according to their randomisation (intention-to-treat analysis).

If one or both of the ANOVA analyses are statistically significant, we will subsequently perform a pair-wise testing based on t-tests:

• Osteosynthesis versus non-surgical management.

• Hemiarthroplasty versus non-surgical management.

• Osteosynthesis versus hemiarthroplasty.

Thus, our protection against the risk of type 1 errors consists on a clear definition of the two primary outcomes and a single analysis ANOVA approach.

We will also conduct the following secondary analyses:

• The above analysis will be conducted for the following two subgroups: valgus-impacted and classical fractures respectively.

• In the osteosynthesis group we will conduct a subgroup analysis comparing patients with intraoperative change to hemiarthroplasty with those without.

• We will repeat the primary analysis as a mixed model for repeated measurements (including data from six months and the predefined covariates: age, ASA-Score, and treatment preference at baseline).

• The number of patients with Constant score ≥ 70 at month 12 for each group (and subgroup) will be compared with Chi-square tests.

The same analyses (except the third) will be performed for the other outcomes (Oxford Shoulder Score, Short Form-36).

Finally, we will perform a per protocol effect analysis in which only patients that were compliant with physiotherapy and training (attending > 75% physiotherapy sessions judged by physiotherapist) will be included.

The same analyses will be performed for the other outcomes (Oxford Shoulder Score, Short Form-36).

A three year follow-up analysis will be reported in a separate publication. The analyses will compare number of patients in each group that died, received shoulder surgery, etc.

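### The primary analysis uses six-month Constant scores in place of missing 12-month scores, which biases the comparison if late recovery or late drop-out differs by arm; the mixed model already planned should be primary

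*Protocol article*

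**What the plan says.** The Outcome measures section of the protocol article defines the first primary outcome as "Constant Disability Scale – total score (0–100 points) at 12 months" and puts the pain subscale, the second, at the same time point. Under Evaluation, the score is collected twice: "Clinical outcome assessment will be performed after six and 12 months by a blinded central physiotherapist". No baseline Constant score is described.

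The Data-analysis section handles missing data in two ways. For late losses: "Patients that drop-out after the six months evaluation will be included in the analysis based on six months data". For early losses: "Drop-out of patients before the six months evaluation cannot be included in the analysis". It applies this to the primary ANOVAs: "We will use the last observation carried forward approach, excluding patients only because of missing data", and labels the result intention-to-treat. If either ANOVA is significant, three pairwise t-tests follow.

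Among the secondary analyses is this: "We will repeat the primary analysis as a mixed model for repeated measurements". It is to include the six-month data and the covariates age, ASA score and baseline treatment preference. The article does not say whether carried-forward values are left out of that model, or whether it has an arm-by-visit term.

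The sample size section allows for losses: "with an assumed standard deviation of 15 points and a loss to follow up of 10 patients in each group".

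**The concern.** A patient who leaves after six months enters the primary analysis with a score from the wrong time point. That score is right for 12 months only if nothing changes in between. The protocol gives no ground for expecting this: it measures at both times, makes the later one primary, and foresees secondary surgery in the non-surgical arm. One arm has no primary operation and the other two have different ones, so the pace of late recovery could well differ between arms.

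At stake is the main estimate for both primary outcomes and the test that opens the pairwise comparisons. The bias can go either way. It shrinks a true difference when the better arm is still improving faster, and enlarges it when the worse arm loses more patients who would have improved. A method that avoids the carry-forward is already in the plan, but only in a supporting role.

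**Working it through.** **1. The plan's own sample size.** Inputs from the sample size section: 80% power, 5% level, 10-point difference, SD 15, 10 lost per group, total 162, so 162/3 = 54 per group and 54 − 10 = 44 evaluable. For a three-group ANOVA with the extreme means 10 points apart and the third midway, the squared deviations sum to 25 + 0 + 25 = 50, and the noncentrality is λ = n × 50/15².
- n = 44: λ = 9.78, power 79.6%.
- n = 45: λ = 10.0, power 80.6%.

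So 3 × (44 + 10) = 162 reproduces with 44 evaluable per group. The strict solution is 45, giving 165. The 162 already writes off 10 patients per group, so carry-forward is not needed to reach the planned power.

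**2. Bias from carrying forward.** Let q be the share of an arm's analysed patients who are carried forward, and g that arm's mean gain from 6 to 12 months. The arm's mean is then too low by q × g, so

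bias in (A − B) = −(q_A × g_A − q_B × g_B).

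The protocol gives neither the gains nor the timing of drop-out. Everything below is assumed, apart from the 10 of 54 in the equal-loss rows. Drop-out is taken as unrelated to the individual patient's gain.

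| Late losses per arm | Gains | Bias (absolute) |
|---|---|---|
| 10 of 54 in both | equal | 0 |
| 10 of 54 in both | differ by 5 | 10/54 × 5 = 0.93 |
| 10 of 54 in both | differ by 10 | 10/54 × 10 = 1.85 |
| 5 late of 49 analysed in both (5 more lost early) | differ by 5 | 5/49 × 5 = 0.51 |
| 5 late of 49 analysed in both (5 more lost early) | differ by 10 | 5/49 × 10 = 1.02 |
| 15 v 5 of 54 | equal, 5 each | (15 − 5)/54 × 5 = 0.93 |
| 10 of 54 in both, all early | any | 0 from this source |

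**3. Effect on the test.** Simulation with 6,000 runs per scenario, SD 15, an assumed correlation of 0.7 between the two visits, and a likelihood analysis of observed scores standing for the mixed model.

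| Scenario | Carry-forward ANOVA | Mixed model, observed data |
|---|---|---|
| True difference 10; gains 5, 15, 10; 10 late losses per arm | estimate 8.1, power 66% | estimate 10.0, power 83% |
| True difference 10; equal gains of 5; 10 late losses per arm | estimate 10.0, power 87% | estimate 10.0, power 83% |
| True difference 10; 10 early losses per arm | estimate 10.0, power 80% | estimate 10.0, power 80% |
| No 12-month difference; gains or late losses unequal | type I error 5.4–6.7% | type I error 4.6–5.4% |

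The third row shows the limit of the remedy: when all losses are early, the two analyses coincide.

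**The case against.** The strongest defence is that the harm is conditional. With equal gains and equal late losses the carry-forward estimate is unbiased, and in that scenario it has slightly more power. The protocol states equal losses per group and gives no sign of how gains would differ. Drop-outs and their reasons are recorded, both visits are described by arm, and the mixed model is pre-specified, so a discrepancy would be seen. All of this stands, and it limits the severity. It does not justify resting the primary analysis on an untested no-change assumption when a less restrictive model on the same data is already planned.

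Four stronger readings are tempting, and the protocol does not support them.

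- **That the mixed model also rescues early drop-outs.** It does not. The Constant score is described only at 6 and 12 months, so a patient lost before six months contributes no outcome. For an analysis of patients' own scores, "Drop-out of patients before the six months evaluation cannot be included in the analysis" is correct. Imputation from baseline data is possible but rests on covariates alone.
- **That carry-forward makes the standard error too small, by √(44/54) = 0.90.** The carried-forward values are real measurements, only at the wrong time, so the usual standard error is valid for what is being averaged. In a check with equal arms, about 19% carried forward, drop-out depending on the six-month score and an assumed 10-point gain, the ANOVA's type I error was 5.0%. The average standard error was 3.25 against an empirical 3.23. The fault is bias.
- **That the intention-to-treat label is simply false.** The same sentence qualifies it by allowing exclusion for missing data. The label needs sharpening, no more.
- **That a patient who dies after six months is given a 12-month score.** The article speaks of drop-out and records deaths separately. It does not say that death counts as drop-out, and the full protocol may settle this.

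**Conclusion.** The point holds for carry-forward after six months. The primary analysis mixes 6- and 12-month scores under a 12-month outcome definition, and the contrast is biased when late gains or late drop-out differ by arm. With the planned 10 of 54 lost per arm, all late, and gains that differ by 5 or 10 points, the bias is about 0.9 or 1.9 points, or 9% to 19% of the 10-point target. With half the losses early it is about 0.5 or 1.0 points. With equal gains and equal late losses it is zero. The gains and the split between early and late losses are assumptions, so this is a range of what could happen and not an estimate of what will. The change is worth making before analysis, but the protocol does not show that the primary result is invalid without it.

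**What to change.** 1. Make the mixed model primary for both Constant outcomes. Fit it to observed 6- and 12-month scores only, stating that no carried-forward values enter, with arm, visit, arm-by-visit and the predefined covariates (age, ASA score, baseline treatment preference).
2. Use its two-degree-of-freedom test of arm at 12 months as the global test in place of the ANOVA F test. Let it gate the three pairwise 12-month contrasts from the same model, in place of the t-tests. Reword the type I error statement, which now rests on the ANOVA.
3. Keep the carry-forward ANOVA as a sensitivity analysis.
4. For patients lost before six months, add a sensitivity analysis with multiple imputation from baseline covariates, and qualify the intention-to-treat label to say who is and is not in the primary analysis.

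The cost is slightly more analysis work and rewording of the testing gate and the type I error statement. No new data are needed and the sample size stays at 162. One side benefit: the Blinding section keeps the analysts blind to allocation only for the primary analysis, so the mixed model would then be run under that blinding.
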